## Methods

### Design

A two-stage partially randomized clinical or preference trial (PRCT), originally described by Rücker [4], was used. The trial protocol was approved by the Research Ethics Board at Ryerson University (Protocol Reference # 2010-085-3). The research performed on participants were in compliance with the Helsinki Declaration. As illustrated in Fig. 1, the PRCT involves two stages for participants’ allocation to treatment. In the first stage, eligible participants that have provided written informed consent are randomized to the random or preference arms of the trial, after obtaining pretest data. Randomization at this stage increases the likelihood that participants in the two arms are comparable in their socio-demographic and clinical profiles, status on pretest outcomes, and expressed preferences for the treatments under evaluation. In the second stage, the method of assignment to treatment differs between the trial arms. In the random arm, participants are randomly assigned to treatment, whereas in the preference arm, participants are allocated to the preferred treatment. This treatment allocation scheme allows comparisons on relevant variables between participants who receive the same treatment on the basis of either chance or preference; the results of these comparisons determine the contribution of preferences.

**Fig. 1 Fig1:**
[figure not shown]
Illustration of the PRCT design

The treatments investigated in the current study are two behavioral therapies that demonstrated efficacy in the management of chronic insomnia: stimulus control therapy and sleep restriction therapy [25]. Eligible consenting participants complete the pretest questionnaire measuring socio-demographic and clinical characteristics, sleep outcomes, perception of the treatments’ attributes and preferences for the behavioral therapies. Participants are randomized to the two trial arms, using sealed opaque envelopes. Participants in the random arm are randomly assigned to the stimulus control therapy or the sleep restriction therapy, using sealed envelopes. Participants in the preference arm are allocated to the treatment they indicate that they prefer. Participants expressing no preferences are randomly assigned to treatment. The outcomes are assessed at four points in time: pretest (i.e. within 2 weeks before treatment); post-test (i.e. within 1 week after treatment completion); 6-month and 12-month follow-up. Data on adherence to treatment are collected prospectively, during the treatment and post-treatment periods. Three strategies are used to minimize attrition: reimbursement for travel expenses to attend the data collection and the treatment sessions, a $10 gift certificate, and telephone call reminders. The calls are made to all participants within 1 week prior to the planned research activity (i.e. attendance at treatment session and data collection).

### Sample

Participants with insomnia are recruited through community media advertisements in local newspapers, radio station, and local newsletters targeting middle-aged and older adults. Flyers advertising the study are distributed to community health centers, hospital outpatient clinics, a leisure complex for older adults and sleep clinics.

Persons with insomnia are eligible for the study if they 1) are non-institutionalized adults (≥40 years of age) as insomnia is prevalent in middle-aged and older adults [26], 2) have the ability to read and write English, and 3) complain of difficulty initiating and/or difficulty maintaining sleep, manifested in sleep onset latency and/or time awake after sleep onset of 30 min or more per night, for a minimum of three nights per week, for a duration of at least 6 weeks [27], ascertained with relevant questions of the Insomnia Interview Schedule [28]. Individuals are excluded if they have: 1) cognitive impairment indicated by a score < 24 on the Mini-Mental State Exam [29] because cognitive impairment interferes with participants’ understanding of and ability to implement the behavioral therapies; and 2) confirmed medical diagnosis of sleep apnea as reported by participants; the behavioral therapies are not recommended for sleep apnea.

The sample size is estimated to attain adequate power to determine the effects of treatment preferences on attrition, adherence, and sleep outcomes. Sample size estimation also considers the repeated measure feature of the design. Within-subject designs require a smaller number of participants than between-subject designs, to achieve the same statistical power [30]. A medium sized effect (0.5) is anticipated on the basis of: 1) results of a systematic review showing that behavioral therapies had moderate-to-large effects on sleep parameters (sleep onset latency and wake after sleep onset) in middle-aged and older adults [31]; and 2) an expected medium effect for the comparison of participants assigned to treatment randomly or congruent with their preferences. A medium effect is anticipated, rather than a small effect as reported in the literature, with the use of a reliable and valid measure of treatment preferences. Applying Cohen’s [32] criteria for an anticipated medium effect size for the main comparison, the inclusion of four groups (i.e. participants allocated to the stimulus control therapy and those allocated to the sleep restriction therapy either randomly or based on their preference), and setting α at .05 and β at .80, the required sample size is 60 per group, for a total of 240 participants to be recruited.

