### Data analysis

In addition to descriptive statistics to characterize the participants in terms of their demographic and clinical characteristics, the following analyses are planned to address the study objectives:Objective 1: Chi-square test will be used to compare the number of participants who withdrew from the study across the four study groups defined by the type of treatment received (stimulus control therapy and sleep restriction therapy) and the method of allocation to treatment (random and preference). One-way analysis of variance will be applied to examine differences in level of adherence (i.e. attendance to treatment sessions and enactment of treatment recommendations), and the pattern of change (estimated with a slope) in the sleep outcomes, across groups.Objective 2: Chi-square test will compare the number of dropouts between participants in the random arm who receive matched and mismatched treatment. Independent samples t-test will examine differences between the matched and mismatched subgroups in levels of adherence (exposure and enactment) to treatment and the pattern of change in the sleep outcomes.

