Despite its advantages, there are some challenges in carrying out a two-stage PRCT. The first challenge relates to the first stage of randomization. Through the process of obtaining informed consent, participants are informed of the two stages and of the method for treatment allocation within each arm. Participants with strong treatment preferences may be unwilling to leave treatment choice to chance and they may desire allocation to the preference arm. If randomized to the random arm, they may react unfavorably [4] and withdraw from the study.

The second challenge in the implementation of the two-stage PRCT relates to the method of treatment allocation applied in the second stage of the trial. At this stage, participants in the random arm are randomized to treatment, yielding a balanced number of participants assigned to the treatment groups. However, the equality of the treatment groups’ sizes is not achieved in the preference arm if most participants choose one treatment over the other. Large differences in group sizes may yield unequal within-group variances; if not addressed with appropriate statistical formula, unequal variances may reduce the power to detect significant treatment and preference effects [35]. The validity of these conclusions is further jeopardized if the pretest comparability of participants is not maintained. Randomization to treatment, applied in the random arm, increases the likelihood of achieving baseline comparability. However, such comparability may not be observed in the preference arm due to possible differences in the profile of participants choosing the alternative treatments under evaluation. Therefore, the baseline comparability of participants assigned to the different treatments randomly or by preference is not maintained, potentially confounding the results.

The third challenge in conducting the two-stage PRCT relates to the reactions of participants assigned to treatment on the basis of chance or preference. Specifically, participants in the random arm may have preferences for the treatments under investigation. Those randomized to the non-preferred treatment may react unfavorably. In contrast, participants in the preference arm may react favorably because they get the treatment they desire. These reactions may influence the participants’ adherence and responses to the allocated treatment.

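### The sample size statement gives β as .80, which means 20% power, and 60 per group cannot be reproduced from the inputs it states

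*Protocol article*

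**What the plan says.** The Sample section of the protocol article opens the calculation with a broad aim: "The sample size is estimated to attain adequate power to determine the effects of treatment preferences on attrition, adherence, and sleep outcomes". It says that the repeated-measures feature was taken into account, but gives no correlation or reduction factor. On the effect it says "A medium sized effect (0.5) is anticipated on the basis of" two grounds: earlier evidence on behavioural therapies, and an expected medium effect of allocation method. It then continues "Applying Cohen’s [32] criteria for an anticipated medium effect size for the main comparison", with "the inclusion of four groups" (two therapies, each allocated randomly or by preference), and "setting α at .05 and β at .80". The result is 60 per group, 240 in all, given both as the required number and as the number to recruit: "β at .80, the required sample size is 60 per group, for a total of 240 participants to be recruited".

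For Objective 1 the Data analysis section plans a chi-square test on withdrawals across the four groups. For the other outcomes, "One-way analysis of variance will be applied to examine differences in level of adherence", and likewise in the pattern of change in sleep outcomes, summarised as a slope. The Design section and the Discussion also describe comparing people who receive the same therapy by chance or by choice. Attrition is itself an outcome, counted at any time after consent, and follow-up runs to 12 months. The Discussion acknowledges that equal group size "is not achieved in the preference arm if most participants choose one treatment over the other".

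**The concern.** Three things in the paragraph do not fit together. β is mislabelled. The effect of 0.5 is medium on Cohen's d scale for two groups, whereas the four-group setting and the planned ANOVA point to Cohen's f, where medium is .25; the text does not say which was used. And neither reading gives 60. In addition, the required number is recruited with no stated margin for loss, in a study that measures loss over 12 months.

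What is at stake is how results will be read. The paragraph is the article's only statement of power, and it claims adequacy for attrition, adherence and sleep outcomes alike. A reader who meets a null result needs to know which comparison, at what effect and with how many analysed, had the power claimed. The answer differs considerably between comparisons.

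**Working it through.** **Inputs from the article.** α = .05 (sidedness not given; two-sided assumed); β = .80 as printed; effect 0.5, metric not named; Cohen's medium; four groups of 60; one-way ANOVA across the four groups.

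**Assumed here, not in the documents.** Attrition of 20% or 30%, equal across groups; a 70:30 split of choices in the preference arm; dropout proportions for the attrition endpoint.

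**Formulas.** Two groups: noncentral t with n₁ + n₂ − 2 df and noncentrality d·√(n₁n₂/(n₁+n₂)). Four groups: noncentral F with 3 and 4n − 4 df and noncentrality 4n·f². Two proportions: normal approximation.

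**Step 1, as printed.** β = .80 is power 1 − .80 = .20. That needs 11 per group for d = .5, or 10 per group for f = .25 with four groups. Neither is near 60, so the printed β is a slip for power .80.

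**Step 2, trying to reproduce 60 at power .80.**
- d = .5, normal approximation: n = 2(1.960 + 0.842)²/0.5² = 62.8, so 63. Exact t: 64 (power .801).
- d = .5, one-sided: 50 to 51.
- Four-group ANOVA, f = .25: 45 (noncentrality 180 × .0625 = 11.25, power .804).
- Four-group ANOVA, f = .5: 12.
- d = .5 between the extreme groups, converted to f under Cohen's minimum or intermediate spread: 89 or 80.
- 2×2 main effect, f = .25: 32 per cell.
- Chi-square, w = .3, 3 df: about 122 in total.

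None gives 60. Only inputs that the article does not state come close: 90% power at f = .25 gives 58; 25% dropout on 45 gives 45/.75 = 60; a correlation of about .25 used as a variance reduction takes 64 to 64 × (1 − .25²) = 60.

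**Step 3, what 240 delivers.** 60 per group falls to 48 at 20% attrition and 42 at 30%; pooled arms of 120 fall to 96 and 84.

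| Comparison | No loss | 20% loss | 30% loss |
|---|---|---|---|
| Four-group ANOVA, f = .25 | 91% | 83% | 77% |
| Random v preference, pooled, d = .5 | 97% | 93% | 90% |
| Same therapy, random v preference, d = .5 | 78% | 68% | 62% |

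**Step 4, unequal choice.** At 70:30 the smaller preference group is .30 × 120 = 36. Its same-therapy comparison, 36 v 60 without attrition, has noncentrality .5 × √(2160/96) = 2.37 and power 65%.

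**Step 5, attrition as an endpoint.** With 120 v 120, dropout of 25% v 15% is detected with 49% power. For 30% v 15%, 121 per arm are needed for 80%, so 120 gives about 80%.

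**The case against.** The strongest reply is that nothing of substance is wrong. The β is a transparent slip. A 0.5 SD effect of allocation method in both therapies gives two group means at +.25 SD and two at −.25 SD, which is f = .25 exactly, so the 0.5 and Cohen's four-group medium can be the same effect. On that reading the planned ANOVA stays at or above 80% power up to about 25% attrition (45 per group). This stands. A reader might infer from the 78%, 68% and 65% figures that the trial is underpowered. The article does not support that: those figures belong to one pairwise contrast, while the omnibus test and the pooled comparison do better.

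A reader might also infer that the repeated-measures saving is simply mistaken because the tests are between groups. That too goes further than the article allows. The sleep outcomes are analysed as per-person slopes, and within-person correlation affects the error variance of a slope and can reduce it. What stands is narrower: no correlation is given, and the saving cannot extend to attendance or attrition.

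Finally, a condensed article may leave an attrition allowance to the full protocol, and 60 may already contain one. That is possible, so the defensible statement is that 60 is not reproducible from what is stated, rather than that 60 is wrong. But the article itself equates the required and recruited numbers. The Discussion's disclosure of unequal preference groups is fair warning, but it is not carried into the calculation.

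**Conclusion.** The concern holds in this form: the printed β is wrong, and 60 per group does not follow from the stated inputs, lying between 45 (f = .25, four groups) and 64 (d = .5, two groups). The metric, the contrast and any attrition allowance are unstated. Of the comparisons of means, only the same-treatment pairwise one falls short of 80% before any loss, and modestly so at 78%. The blanket claim of adequate power is least secure for attrition, where about a 15-point gap (30% v 15%) is needed for 80%.

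The β error depends on no assumption. The sample size results assume two-sided α .05. The figures under attrition, the 70:30 split and the dropout proportions are illustrations, because the article gives no such rates.

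**What to change.** In the Sample section:

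1. Replace the printed β by β = .20 (power .80).
2. Say whether 0.5 is d or another metric, and which contrast was sized. State the attrition assumption, or say that 60 already includes one, so that 60 can be reproduced.
3. Report the power that 240 gives for each planned comparison, with and without attrition, as in the table above. Add the effect of an uneven choice of therapy on the same-treatment comparison, and label assumed rates as such.
4. Support the within-subject saving for the slope outcomes with a stated correlation, or do not rely on it. Do not apply it to attendance or attrition.
5. Limit the claim of adequate power for attrition to the difference that 240 can detect.

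The cost is wording, and a less favourable stated power for the pairwise comparison. No participants are added, and allocation and analysis are unchanged, which matters because the study is already in its last stage of data collection.

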## Discussion

The study is in its final stage of collecting outcome data for the 12-month follow-up. To date, 421 persons showed interest and agreed to undergo initial screening.

The study extends previous research on the role of treatment preferences in intervention evaluation research in two ways. First, the two-stage PRCT design is applied, which is considered the most appropriate design for evaluating the influence of treatment preferences because of its advantages. The PRCT design is useful to dismantle the influence of treatment preferences from the impact of treatment on attrition, adherence and outcomes. This is accomplished by creating groups of participants who receive the same treatment randomly or by preference; comparison of these groups indicates the contribution of treatment preferences to attrition, adherence and outcomes. The PRCT design also minimizes the potential for selection bias resulting from non-comparability of participants assigned to different treatments randomly or on the basis of preference [3, 10]. The advantages stem from the randomization of participants to the random and preference arms in the first stage of assignment. Randomization at this stage maintains a balanced number and comparability on baseline characteristics of participants allocated to the two arms of the trial. This initial comparability reduces the potential for selection bias and confounding of the effects of treatments and preferences. It also enhances the validity of conclusions regarding the effectiveness of the treatments and the influence of preferences on adherence and outcomes of the treatments under investigation.

Second, the study uses a systematic method for assessing treatment preferences. The method begins by providing information on the treatments’ goals, components, activities, mode and dose of delivery, benefits and risks; it proceeds by having participants rate each treatment relative to four attributes prior to indicating their preferences. The TAP measure operationalizes this systematic method, has sound psychometric properties, and is expected to accurately capture participants’ preferences.

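### Sixty per group from 240 recruits holds only if preference-arm choices split evenly; an uneven split shrinks the less-chosen group and weakens its chance-versus-choice comparison

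*Protocol article*

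**What the plan says.** The Sample section sizes the trial for four groups, described as "participants allocated to the stimulus control therapy and those allocated to the sleep restriction therapy either randomly or based on their preference". The inputs are an effect of 0.5 ("A medium sized effect (0.5) is anticipated on the basis of") and error rates given as "setting α at .05 and β at .80", where the second figure can only mean power of 0.80. The result is that "the required sample size is 60 per group, for a total of 240 participants to be recruited".

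The Design section lets stated preference decide treatment in the preference arm; only participants without a preference are randomised to a therapy. It also names what the design is for: "comparisons on relevant variables between participants who receive the same treatment on the basis of either chance or preference", from which the contribution of preferences is to be read. The Discussion repeats that purpose.

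On group sizes, the Discussion says of the first stage that "Randomization at this stage maintains a balanced number and comparability on baseline characteristics of participants allocated to the two arms of the trial", and of the second that "participants in the random arm are randomized to treatment, yielding a balanced number of participants assigned to the treatment groups". For the preference arm it concedes that "the equality of the treatment groups’ sizes is not achieved in the preference arm if most participants choose one treatment over the other". It then ties the loss of power to unequal within-group variances that are not handled by a suitable formula.

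**The concern.** The requirement is stated per group, but the design controls the size of only two of the four groups. The other two share whatever number the preference arm holds, in a ratio that participants set. Going from 60 per group to 240 in total therefore assumes an even split without saying so, and the Discussion itself doubts that assumption. No expected split, inflation or minimum for the smaller group enters the calculation.

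At stake is the same-therapy comparison for whichever therapy fewer people choose. The Discussion suggests that the difficulty is one of variances and can be met in the analysis. A small group costs precision even when variances are equal, and no choice of test restores it.

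**Working it through.** **Inputs.** From the article: effect 0.5, alpha 0.05, power 0.80, four groups, 60 per group, balanced arms, balanced therapies within the random arm. Assumed: two-sided test, common standard deviation of 1, arms of 240/2 = 120, 60 randomised to each therapy, all 240 analysed, a continuous outcome, and the preference-arm split.

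**The plan's own figure.** 4 × 60 = 240 is correct as multiplication. The 60 is not exactly recovered from the stated inputs: a two-group comparison at d = 0.5 needs 63 per group (normal formula) or 64 (t test), and a four-group ANOVA at f = 0.25 needs 45. A four-group ANOVA in which one group alone differs by 0.5 does reach 80.6% at 60 per group, but the article states no such pattern. How 60 was derived is a separate matter; here it is taken as given.

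**How often 240 gives four groups of 60.** Of 120 people in the preference arm, exactly 60 must end up in each therapy. Even if each chose independently with probability 0.5, the chance is C(120, 60)/2^120 = 0.073. Small departures matter little, so the next step is how power changes with the split.

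**Same therapy, chance (60) v choice (b).** Noncentrality is δ = 0.5/√(1/60 + 1/b) on 58 + b degrees of freedom. For b = 36, δ = 0.5/√(0.01667 + 0.02778) = 2.37, which gives 65.1%.

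| Final preference-arm split | Less-chosen group | Power | More-chosen group | Power |
|---|---|---|---|---|
| 50:50 | 60 | 77.5% | 60 | 77.5% |
| 55:45 | 54 | 75.3% | 66 | 79.4% |
| 60:40 | 48 | 72.5% | 72 | 81.0% |
| 70:30 | 36 | 65.1% | 84 | 83.6% |
| 80:20 | 24 | 53.4% | 96 | 85.5% |

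**Participants without a preference.** If a share q has none and is randomised evenly, and a share p of the rest prefers the less popular therapy, the smaller group is 120 × [(1 − q)p + q/2]. With q = 0.20 (assumed):
- p = 0.30: 120 × (0.24 + 0.10) = 40.8, about 41; power 69%.
- p = 0.20: 120 × (0.16 + 0.10) = 31.2, about 31; power 61%.

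For a given ratio of preferences, everyone stating a preference is therefore the worst case for imbalance.

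**Random arm v preference arm.** For 120 v 120, δ = 0.5/√(2/120) = 3.87 and power is 97.1%, whatever the split.

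**Planned four-group ANOVA.** Noncentrality is λ = Σ nᵢ(μᵢ − μ̄)² on 3 and 236 degrees of freedom.
- Both preference groups shifted by 0.5: λ = 240 × 0.25² = 15 at every split; power 91.2%.
- Only the less-chosen preference group shifted: λ = 0.25 × b(240 − b)/240. This is 11.25 at b = 60 (80.6%) and 7.65 at b = 36 (62.4%).
- Only the more-chosen preference group shifted: at 84, λ = 0.25 × 84 × 156/240 = 13.65 (88.2%).

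**Difference in the preference effect between therapies.** The standard error of the interaction contrast is √(1/60 + 1/60 + 1/a + 1/b), with a and b the two preference-group sizes. At 60 and 60 it is 0.258, so δ = 0.5/0.258 = 1.94 and power is 49% for a 0.5 difference. It is lower at any uneven split (45% at 84 and 36).

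**The case against.** The strongest reply is that the article never promises 80% power for each within-therapy contrast. It sizes for a main comparison with four groups, Objective 1 compares random with preference allocation, and the Data analysis section plans four-group tests, not pairwise ones. The within-therapy contrast has only 77.5% even at 60 v 60, so an even split would not bring it to 80% either. This stands: the benchmark here is the stated group size and the power it would have given, not a broken promise of 80%.

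A reader might infer that the whole trial is underpowered. The figures do not support that. The arm comparison keeps 97%, and the four-group test keeps 91% when both preference groups shift by 0.5. The four-group test loses power when the less-chosen preference group alone differs and gains when the popular one alone differs.

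A reader might also take the shortfall as a fact. The article gives no split; near 50:50 the loss is trivial, and it becomes material only at about 70:30. Nor does the article hide the issue, since the Discussion foresees unequal groups and reduced power. What it leaves out is the direct effect of group size, and the Sample section does not carry the imbalance into the stated numbers.

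Finally, one could fear that significance in one therapy and not in the other will be read as a therapy-specific preference effect. Nothing in the article plans that inference, so it is a caution and not a fault in the plan.

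**Conclusion.** The point holds in a limited form and is minor. The Sample section turns a per-group requirement into a total that delivers it only under an even split, which the design does not control and the Discussion doubts. If choices are uneven, the less-chosen preference group falls below 60, and its chance-versus-choice comparison drops from 77.5% to 73%, 65% or 53% at final splits of 60:40, 70:30 or 80:20. Some participants having no preference would reduce the loss.

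The size of the loss rests on an assumed split, d = 0.5, equal variances, a two-sided test and all 240 analysed. Objective 1's overall comparison is not put at risk. With 12-month follow-up in its final stage, the matter now bears on how group sizes and power are described and how within-therapy results are read.

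**What to change.** 1. In the Sample section, replace the statement of 60 per group and 240 in total with: *120 per trial arm; about 60 per therapy in the random arm; preference-arm group sizes determined by choice.*
2. State power for the arm-level contrast (120 v 120), and give within-therapy power at the observed split or, failing that, over 50:50 to 80:20.
3. In the Discussion, add that unequal group size itself reduces power for the less-chosen therapy, whatever the variances.
4. If the therapies are compared on the preference effect, use the allocation-by-therapy interaction estimate with its confidence interval, and note its low power (about 49% or less for a 0.5 difference).

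The cost is some wording and a small table, with no extra participants. The downside is a less favourable stated power for the less-chosen therapy.
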